### Supervised Exercise Training

In this study, 10 days after completing baseline testing, eligible participants will begin the 2-week supervised exercise training. Participants in each condition will participate in 10 sessions of exercise performed over a 12-day period (ie, Monday to Friday over 2 weeks with Saturday and Sunday as rest days). Seven of these sessions will be supervised in the laboratory and will last approximately 30 to 60 minutes each, while 3 sessions will be conducted at home to foster independence and work through plausible barriers participants may encounter in the future. Each supervised exercise session will occur one-on-one with a counselor and will consist of an exercise component (ie, HIIT or MICT) and 10 minutes of counseling. Participants will be exposed to a variety of exercise formats within their given modality (ie, stationary cycling, treadmill walking, elliptical machine, and outside walking). For 4 of the 7 supervised sessions, participants will be able to self-select the exercise format to encourage autonomy. A total of 2 sessions will be performed on the cycle ergometer during which in-task affect and enjoyment will be assessed to more precisely control exercise intensity and control for the influence of exercise format on enjoyment. The exercise prescriptions for each condition will be progressive in nature (see Table 1) and matched for estimated external work.

**Table 1 table1:** Two-week intervention exercise prescription.

High intensity interval training^a^	Training day/activity completed	Continuous moderate intensity training^b^
4 intervals	Day 1^c^	20 minutes
5 intervals	Day 2^d^	29 minutes
6 intervals	Day 3^e^	33 minutes
Home day, 6 intervals prescribed	Day 4^e^	Home day, 33 minutes prescribed
7 intervals	Day 5^e^	36 minutes
8 intervals	Day 6^e^	40 minutes
Home day, 8 intervals prescribed	Day 7^e^	Home day, 40 minutes prescribed
9 intervals	Day 8^e^	43 minutes
Home day, 9 intervals prescribed	Day 9^e^	Home day, 43 minutes prescribed
10 intervals	Day 10^c^	50 minutes

^a^One high intensity interval consists of 1 minute at ~80-90% VO_2_ peak and one minute ~40% VO_2_ peak.

^b^Moderate intensity continuous exercise consists of continuous exercise at ~45-55% VO_2_ peak.

^c^Stationary bike.

^d^Outdoor walking (hills for HIIT, flat for MICT).

^e^Participant choice (includes stationary bike, treadmill, elliptical, outdoor walking).

### High-Intensity Interval Training Protocol

HIIT involves sessions of 4 to 10 ×1-minute high-intensity intervals (cycling *sprints*, uphill treadmill walking, uphill outdoor walking, and elliptical machine) at approximately 80% to 90% peak oxygen uptake (VO_2_ peak), interspersed with 1-minute rest periods at approximately 40% VO_2_ peak. Results from the pilot study preceding this randomized controlled trial demonstrated that individuals with prediabetes respond well to this protocol [30].

### Moderate-Intensity Continuous Training Protocol

MICT involves sessions of 20 to 50 minutes continuous moderate-intensity exercise (cycling, treadmill walking, outdoor walking, and elliptical machine) at approximately 45% to 55% VO_2_ peak. This prescription of MICT matches the progression of HIIT (percent increase over time) and modeled the exercise program that has been shown to prevent the progression of prediabetes to T2D (ie, primarily walking; [11]). An intensity of approximately 45% to 55% VO_2_ peak, which approximates brisk walking [45,46], has been shown to improve cardiometabolic health in several large trials [47,48] and is commensurate with the level of intensity recommended by the American College of Sports Medicine [49] for inactive adults to promote exercise adherence.

### Transition to Independent Exercise

The 2-week supervised exercise training program will incorporate 3 unsupervised sessions to enable participants to practice engaging in exercise independently. Following completion of the 2-week program, participants will be asked to engage in their randomized exercise protocol (ie, HIIT or MICT) a minimum of 3 times per week for the next 12 months. Specifically, participants in HIIT will be prescribed a 5-minute warm-up, 10 ×1-minute high-intensity intervals, and a 5-minute cooldown. Participants in MICT will be prescribed 50 minutes of moderate-intensity exercise.

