#### Secondary Outcomes

##### Physical Activity

Objectively measured purposeful MVPA adherence (ie, MVPA10+) will be assessed by triaxial accelerometry (Actigraph GT3X-BT, Actigraph, Pensacola, Florida, USA) at baseline and 3-, 6-, 9-, and 12-month follow-up. MVPA10+ is appropriate for measuring purposeful exercise [51] and provides a conservative estimate of exercise adherence. Participants will be instructed to wear the accelerometer on their right hip for 7 consecutive days at each measurement time point. Participants will be instructed to remove the accelerometer during sleep and for water-based activities. Accelerometers will be initialized and downloaded using ActiLife version 6.11. Epoch lengths will be specified at 5 seconds and will be summed as counts per minute. Nonwear time will be classified as 90 minutes of consecutive zeros, allowing for nonzero counts up to 2 minutes; if no counts are detected during the 30-minute counts before and after this interval [52], these data will be classified as nonwear time and excluded from analysis. Participants must have a total of ≥10 hours of valid wear time per day to be included in the analyses [53]. Our pilot work confirmed that recovery intervals during HIIT register as moderate-to-vigorous activity, not interruptions to physical activity. Freedson cut points [54] will be used to identify time spent in moderate (1952-5724 counts/min), vigorous (≥5725 counts/min), and MVPA (≥1952 counts/min) during wear time on valid wear days. Time spent in the various intensities will be averaged across valid wear days and multiplied by 7 to provide a weekly estimate of physical activity at each measurement time point. Purposeful exercise will be operationalized as minutes spent in MVPA10+ [54], in line with physical activity guidelines, which specify that bouts of physical activity should be accumulated in bouts of 10 minutes or more. Furthermore, given that participants in HIIT are prescribed 75 minutes of purposeful exercise per week (ie, 3×25-min HIIT sessions) and participants in MICT are prescribed 150 minutes per week (ie, 3×50-min MICT sessions) and that physical activity guidelines highlight the equivalency of 75 minutes of vigorous exercise and 150 minutes of moderate exercise, additional supplemental analyses will be conducted, whereby each vigorous minute of exercise within the identified MVPA10+ bouts will be credited as 2 minutes. This approach was carefully considered for the adherence measure and justified in the grant application for this trial. As such, this modified MVPA10+ outcome represents an appropriate measure of purposeful exercise [51] and allows for a direct assessment of adherence to HIIT or MICT.

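### The stated 25-minute HIIT session (75 min/week) is not the sum of its listed parts, and the 75/150 equivalence it supports does not make full adherence score equally in the two arms

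*Protocol article*

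**What the plan says.** All references are to the protocol article.

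- **Transition to Independent Exercise** lists the HIIT session by its parts: "participants in HIIT will be prescribed a 5-minute warm-up, 10 ×1-minute high-intensity intervals, and a 5-minute cooldown". The frequency is "a minimum of 3 times per week for the next 12 months". Neither a recovery time nor a session total is given. For the comparator: "Participants in MICT will be prescribed 50 minutes of moderate-intensity exercise".
- **Supervised Exercise Training**, Table 1 footnote a, makes recovery part of the interval: "One high intensity interval consists of 1 minute at ~80-90% VO_2_ peak and one minute ~40% VO_2_ peak". **High-Intensity Interval Training Protocol** describes the intervals as "interspersed with 1-minute rest periods at approximately 40% VO_2_ peak".
- **Physical Activity** (under Secondary Outcomes) states the weekly dose: "participants in HIIT are prescribed 75 minutes of purposeful exercise per week (ie, 3×25-min HIIT sessions"), and for the comparator "participants in MICT are prescribed 150 minutes per week (ie, 3×50-min MICT sessions").

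The Physical Activity section sets these two weekly doses beside the guideline that treats 75 vigorous minutes as equal to 150 moderate minutes. From that pairing it derives a supplemental analysis in which vigorous minutes inside MVPA10+ bouts count double, and it says that the modified measure allows adherence to either regimen to be assessed directly.

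**The concern.** A stated intervention dose should equal the sum of its stated parts. Here one section lists parts and another gives a total, and the two do not agree.

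The total is also put to use. The double-credit measure puts two unequal prescriptions on one scale, so that a participant who does everything asked scores the same in either arm. That works only if 75 HIIT minutes convert to 150 credited minutes, which requires all 75 to be vigorous. The prescription has only ten high-intensity minutes per session. If the conversion falls short, a fully adherent HIIT participant can score below a fully adherent MICT participant, and a difference between arms on this measure would partly reflect how the scale is built.

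**Working it through.** **Inputs.** Warm-up 5 min, 10 intervals of 1 min, cooldown 5 min, at least 3 sessions per week (Transition to Independent Exercise). Recovery 1 min per interval (Table 1 footnote a; High-Intensity Interval Training Protocol). Stated doses 25 min and 75 min/week for HIIT, 50 min and 150 min/week for MICT (Physical Activity).

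**Step 1: reproduce the stated figures.** MICT: 3 × 50 = 150 min/week, which agrees. HIIT: 3 × 25 = 75 is correct as a product, but the 25 has to come from the parts.

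**Step 2: session length = warm-up + work + recovery + cooldown; weekly dose = 3 × session.**

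| Reading | Session (min) | Weekly (min) | Difference from 75, as % of this weekly total | Share of MICT's 150 |
|---|---|---|---|---|
| As listed, no recoveries | 5 + 10 + 5 = 20 | 60 | 15/60 = 25% | 40% |
| Nine recoveries between ten intervals | 5 + 10 + 9 + 5 = 29 | 87 | 12/87 = 13.8% | 58% |
| Ten two-minute units (Table 1) | 5 + 20 + 5 = 30 | 90 | 15/90 = 16.7% | 60% |
| Intervals and recoveries only | 19 to 20 | 57 to 60 | 18/57 = 32% to 25% | 38% to 40% |

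The last row leaves out the warm-up and cooldown that the prescription includes, so the first three rows set the range of about 14-25%. The stated share is 75/150 = 50%.

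With ten intervals, 25 minutes arises only as 5 + 20, counting one of warm-up and cooldown and dropping the other. An eight-interval session with seven recoveries, warm-up and cooldown also gives 5 + 8 + 7 + 5 = 25, but ten intervals are prescribed.

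**Step 3: the double-credit measure.** Credited minutes per week = total MVPA10+ minutes + vigorous minutes, because each vigorous minute counts once more.

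- What the equivalence needs at 75 min/week: 75 + V = 150, so V = 75. Every minute must be vigorous.
- What is prescribed at about 80-90% VO2 peak: 3 × 10 = 30 min/week, which is 30/75 = 40% of that.

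Assume (a) that only the ten work minutes per session register as vigorous, (b) that the whole session counts as MVPA10+, and (c) that MICT minutes register as moderate. For a HIIT session of T minutes, the weekly credit is 3 × (T + 10):

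| T (min) | Credited min/week, full HIIT adherence | MICT, full adherence |
|---|---|---|
| 20 | 3 × 30 = 90 | 150 |
| 25 | 3 × 35 = 105 | 150 |
| 29 | 3 × 39 = 117 | 150 |
| 30 | 3 × 40 = 120 | 150 |

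Assumption (b) has partial support in the article, which reports from pilot work that "recovery intervals during HIIT register as moderate-to-vigorous activity, not interruptions to physical activity". It says nothing of the kind about warm-up and cooldown. Nor does it say how many HIIT minutes reach the vigorous cut point, so (a) cannot be checked.

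**The case against.** The strongest reply has four parts.

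1. **A convention could give 25.** The stated figure is described as purposeful exercise, not total session time, so part of the light phases may have been left out: ten two-minute units plus one five-minute phase. This stands to the extent that one cannot say no reading gives 25. But no section states such a convention, and both phases are prescribed.
2. **The 20-minute reading is weak.** Participants continue their randomized protocol, which includes recoveries, so the list is probably abbreviated. This is fair. The more natural comparison is then 25 against 29-30, a gap of 14-17%. The mismatch narrows but remains.
3. **No analysis takes 25 or 75 as an input.** The crediting rule acts on measured minutes and is the same whatever the session length. This is correct. The figure enters the rationale for the measure and its interpretation, not its computation.
4. **The 75 minutes are not called vigorous.** True, but the article sets them directly against the guideline's 75 vigorous minutes and concludes that the measure assesses adherence directly in both arms. That conclusion needs the equivalence.

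A reader might infer more than the document supports:

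- **That the main results are affected.** The VO2 peak outcome and the sample size do not use the figure. Self-reported adherence is sessions done over sessions prescribed, with no 25-minute threshold.
- **That participants were told 25 minutes, or given a wrong dose.** Nothing shows this. The counselor manual and the intervention outline are not at hand.
- **That the trial claims equal benefit in half the time.** It does not. It refers to lower time commitments for HIIT, which holds at 60, 87 or 90 against 150 min/week.

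**Conclusion.** The point holds, with limited reach. The stated 25 min/session and 75 min/week match no breakdown in the article. The components give 20 or 29-30 min (60 or 87-90 min/week), a gap of about 14-25%. The article does not settle which statement is right, so the gap measures disagreement and is not an error against a known true dose.

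The consequence is confined to the supplemental double-credit MVPA10+ analysis. Under assumptions (a) to (c), full adherence earns about 90-120 credited min/week in HIIT against 150 in MICT, a shortfall of 30 to 60 min/week, or 45 at the stated 25 minutes. The shortfall would shrink if recovery minutes also registered as vigorous, and would be larger for the 25- to 30-minute sessions if warm-up and cooldown did not register as MVPA. The equal scoring implied by the 75/150 pairing therefore does not follow from the prescription, even if 25 minutes is taken as correct.

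**What to change.** 1. Reconcile Supervised Exercise Training (Table 1 footnote a), High-Intensity Interval Training Protocol, Transition to Independent Exercise and Physical Activity. State the independent-phase HIIT session once, as warm-up, work, recovery and cooldown, with a total equal to its parts and reflecting what participants were actually given. Use that total wherever a weekly dose is quoted.
2. If the 25 minutes rests on a counting convention, state the convention.
3. Restate or qualify the 75/150 equivalence and the claim that the modified measure assesses adherence directly in both arms. When reporting the supplemental analysis, give the credited minutes that full adherence would earn in each arm under stated assumptions, so that a difference between arms can be read against them.

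The cost is a check against the counselor manual and a text correction. Data collection ended in March 2017, so the regimen cannot change. The article describes analysis as under way, and the rationale and interpretation can still be corrected. No planned model and no primary result has to change.

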### Exercise Counseling

To assist participants with the transition to independent exercise and to promote long-term exercise adherence, participants in both conditions will receive a brief behavioral exercise counseling intervention built into the 2-week supervised training program. The counseling involves 10 minutes of one-on-one structured discussion at the end of each supervised exercise session, totaling 70 minutes over the 2 weeks. Participants will see the same counselor each session to bolster rapport. A detailed description of the BCTs used in the behavioral intervention and the social cognitive mechanisms they are hypothesized to target is reported elsewhere ([name] et al, unpublished data). Participants will receive a worksheet for each of the 3 home-based sessions, each reviewing specific behavior change constructs.

In summary, the key aims of the behavioral exercise counseling are to:

Enhance confidence to perform the exercise (ie, task self-efficacy): providing instruction on how to perform the behavior, opportunities to practice engaging in exercise, helping participants identify physiological cues associated with the assigned exercise intensity, sharing the success stories of similar individuals, and providing positive support.Increase confidence to self-manage exercise (ie, self-regulatory efficacy): providing opportunities to practice self-monitoring behavior, preplan exercise behavior, work through exercise barriers, and practice independent exercise.Increase awareness of the psychological and physiological outcomes associated with exercise engagement (ie, outcome expectations): through education and drawing on the experiences of similar individuals and of the participant throughout the 2-week intervention.

The counseling will follow a semistructured format, targeting specific psychological and behavioral constructs each session, while allowing the participants to share their questions and concerns. The content of the program, tools, and materials to be used; session description; and the underlying theoretical constructs are presented in Multimedia Appendix 2.

### Mobile Phone–Based Self-Monitoring Application

To promote exercise adherence after the 2-week intervention, participants will be provided with a self-monitoring mobile application (app; [50]). The counselor will create the participant’s profile on the app and will show the participant how to navigate through the app on both a smartphone and a computer. Participants will be encouraged to monitor their exercise behavior daily (ie, record exercise into the app, hereon in referred to as *check-ins*) regardless of whether purposeful exercise was planned or completed that day. Participants will be permitted to record 4 nonexercise days within the app per week, coinciding with the prescribed 3 bouts of planned exercise for each week. Once all 4 *rest days* had been used, participants will record a *missed session* on days on which no exercise is completed.

Participants will be reminded to record their exercise behavior each day via an automated SMS text message sent from the app if they have not checked in by 9:00 pm. Participants will be informed that the counselor is able to view their exercise behavior through the counselor portal of the app. In the event of 3 consecutive missed check-ins, the participant will be contacted by the counselor via the app messaging function. During the 12-month follow-up period, the participant will be messaged monthly using the app messaging system on months with no scheduled follow-up appointments (months 1, 2, 4, 5, 7, 8, 10, and 11). These SMS text messages will target verbal persuasion, performance accomplishment, vicarious experience, awareness of physiological and affective cues, social support, self-monitoring, relapse prevention, and action planning.

### Outcomes and Measures

A timeline for when each measure was assessed is provided in Multimedia Appendix 1.

#### Primary Outcomes

The primary outcome is cardiorespiratory fitness determined by measuring VO_2_ peak at 6- and 12 months postrandomization. VO_2_ peak will be assessed by a continuous incremental ramp maximal exercise test on an electronically braked cycle ergometer (Lode Excalibur, The Netherlands). Expired gas will be collected continuously by a metabolic cart (Parvomedics TrueOne 2400, Salt Lake City, Utah, USA) that is calibrated with gases of known concentration and a 3.0 L syringe before every test. The test begins with a 4-minute warmup at 30 Watts, after which Watts increase by 1 every 4 seconds (15 Watts per minute). Verbal encouragement will be provided to the participant throughout the test. The test will be terminated upon volitional exhaustion or when revolutions per minute fall below 50. VO_2_ peak is defined as the highest 30-second average for VO_2_ (in L/min and mL/kg/min). Criteria for achieving VO_2_ peak are (1) respiratory exchange ratio >1.15; (2) plateau in VO_2_; (3) reaching age-predicted heart rate (HR) peak (220-age); and/or (4) volitional exhaustion. A Polar chest strap, which is integrated with the metabolic cart and cycle ergometer software (Lode Exercise Manager), will capture HR. HR peak and peak power output will be recorded as the highest values attained in the test. Cardiorespiratory fitness will be assessed at baseline and 6- and 12-month follow-up.

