### Baseline Testing and Randomization

Baseline testing will last approximately 150 minutes. Participants will be provided with a detailed consent form and will be invited to ask any questions. After written consent is obtained, weight, height, and blood pressure will be taken and a 7-day physical activity recall interview [44] will be conducted to confirm eligibility.

Eligible individuals will be stratified based on sex and then randomly assigned to either the HIIT or MICT exercise conditions. An external statistician, who has no other involvement in the trial, will generate random allocation sequences, which will be linked to an interactive Web page. Permuted blocks of random size will be used. Once an individual is identified as eligible, the research coordinator will access the password-protected Web page, and after entering requisite information on patient eligibility and sex, participants will be randomly allocated. Participants and researchers will be aware of group allocation. Following group assignment, participants will have a fasting blood sample taken, consume a 75 g glucose drink as part of a modified oral glucose tolerance test, complete several Web-based questionnaires, have a second blood sample taken 30 minutes following the glucose drink consumption, undergo a body composition scan, and complete a maximal cardiorespiratory fitness test to exhaustion on a cycle ergometer. At the end of the session, participants will be provided with an accelerometer to wear for 7 consecutive days, commencing the day after baseline testing. Participants will be shown how to wear the device and will be instructed to remove the device while sleeping or for water-based activities. In addition, instruction will be provided to remind participants how to correctly wear the accelerometer. Short message service (SMS) text messages or emails will be sent on days 1, 3, and 5 of monitoring to remind participants to wear the device (see Multimedia Appendix 1 for study measures).

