### Statistical Procedures

#### Sample Size

The a priori sample size was derived in relation to the primary outcome for this trial, cardiorespiratory fitness assessed at 6 and 12 months. To calculate the sample size, a pooled mean of 20.8 mL/kg/min and a SD of 4.0 mL/kg/min were used based on our previous pilot study [30]. At the time of study design, the meta-analyses of Weston et al [69] reported that supervised HIIT led to approximately twice (approximately 19%) the improvement in VO_2_ peak as compared with MICT (approximately 10%) in participants with lifestyle-induced metabolic disease. We, therefore, used a 9% difference between HIIT and MICT as a meaningful exercise-induced increase in our population of interest, corresponding to a Cohen *d* effect size of 0.48 (or Cohen *f* of 0.24). Using these data, with a two-tailed alpha of .05 and 80% power, assuming a medium correlation among repeated measures of *r*=.5, it is calculated that 15 participants are required per group for a significant within-between interaction (calculated using G*Power v3.1; Department of Psychology, University of Duesseldorf).

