#### Proposed Data Analyses

Preliminary analyses will be conducted to test for univariate and multivariate outliers and to test for normality. Data transformations will be conducted if required. Variance between the conditions in baseline outcome variables will be examined. Data will be analyzed on an intention-to-treat basis, with individuals retained within their randomized groups regardless of participation. All significance tests will be assessed at a 5% level of significance and effect sizes will be reported. Sensitivity analysis will be conducted to examine the impact of missing data. We will account for missing data by performing multiple imputation by chained equations to determine whether the results are impacted [74].

Mixed-effects regression with baseline as a covariate and 6- and 12-month outcomes as dependent variables will be used to examine differences in cardiorespiratory fitness between HIIT and MICT. Physical activity behavior assessed by accelerometer will be analyzed similarly but will include 3-, 6-, 9-, and 12-month time points. Mixed-effects regression using baseline and all other time points will be used to determine whether the treatments result in a significant change from baseline.

The mediating effects of task self-efficacy, self-regulatory efficacy, concurrent self-regulatory efficacy, outcome expectations, and self-monitoring will be examined using the INDIRECT macro developed by Preacher and Hayes [75]. The macro computes the following steps simultaneously: (1) regression coefficients for the impact of the intervention on the potential mediators; (2) the association between changes in the mediators and changes in the outcome variable; and (3) the total effects, direct effect, and indirect intervention effects. Bias-corrected bootstrapped 95% asymmetrical CIs will be computed for the indirect effect. Significant mediation will be established if the CIs do not include zero. Multiple mediation models will be computed for MVPA at 12-month follow-up and cardiorespiratory fitness at 12-month follow-up.

A series of mixed-effects regressions will be conducted to examine changes over time between groups in anthropometrics, body composition, biochemical markers, CGM, and additional psychological constructs.

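### VO2peak is primary at both 6 and 12 months with every test at 5% and no deciding contrast named (error about 8–10% if each visit is tested separately); the stated model also leaves out the sex stratum, at a small cost in precision

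*Protocol article*

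**What the plan says.** **Primary outcome.** Primary Outcomes reads: "The primary outcome is cardiorespiratory fitness determined by measuring VO_2_ peak at 6- and 12 months postrandomization". The first item under Small Steps for Big Changes Objectives likewise compares the arms at both times. Neither section ranks the visits.

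**Unit.** The same section gives the measurement definition: "VO_2_ peak is defined as the highest 30-second average for VO_2_ (in L/min and mL/kg/min". Sample Size uses only the weight-relative unit: "a pooled mean of 20.8 mL/kg/min and a SD of 4.0 mL/kg/min were used".

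**Analysis.** Proposed Data Analyses plans "Mixed-effects regression with baseline as a covariate and 6- and 12-month outcomes as dependent variables" to compare HIIT with MICT, and adds "All significance tests will be assessed at a 5% level of significance and effect sizes will be reported". It names no joint test, averaged effect, deciding visit or multiplicity rule. A further mixed model, using baseline and all other time points, addresses change from baseline. The mediation models take 12-month fitness alone.

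**Randomisation.** Baseline Testing and Randomization says: "Eligible individuals will be stratified based on sex and then randomly assigned to either the HIIT or MICT exercise conditions". Baseline is the only covariate named for the primary model.

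**The concern.** A mixed model with two post-baseline visits can yield several treatment tests: a difference at 6 months, one at 12 months, their average, a 2-df joint test, or a treatment-by-time interaction. The article calls the outcome at both visits primary and allows each test the full 5%, but does not say which of these decides. If either visit can carry the primary claim, the error rate for that claim exceeds the "with a two-tailed alpha of .05 and 80% power" on which the trial was sized.

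The gap matters more here than in a blinded trial still recruiting. Participants and researchers know the allocation, and the Results section reports that data collection is complete and analysis underway. A contrast not yet named could therefore be picked after results are seen.

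The sex stratum is a separate and smaller matter. When randomisation is balanced within sex and sex predicts the outcome, a model without sex attributes that variation to noise and overstates the standard error of the treatment effect.

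**Working it through.** **1. The plan's own figure.** Inputs from Sample Size: f = 0.24, r = 0.5, alpha 0.05, power 80%, within-between interaction. For two groups and m occasions, λ = f²·N·m/(1 − r), with (m − 1) and (N − 2)(m − 1) degrees of freedom. With m = 3 (baseline, 6 and 12 months) and N = 30, λ = 0.0576 × 30 × 3 / 0.5 = 10.37 on 2 and 56 df, and power is 0.81. The stated 15 per group reproduces (m = 2 gives 19, m = 4 gives 13). The trial was therefore sized on one F test with baseline as an occasion. The analysis section instead uses baseline as a covariate, so the sized test does not itself identify the deciding one.

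**2. Error rate if each visit is tested at two-sided 5%.** The rate is P(|Z₁| > 1.96 or |Z₂| > 1.96), with Z₁ and Z₂ bivariate normal with correlation ρ. If all three occasions correlate at r = 0.5, the between-visit correlation after baseline adjustment is (r − r²)/(1 − r²) = 0.25/0.75 = 0.33. Higher values are assumed, to show the range.

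| ρ between visits | Chance of at least one false positive |
|---|---|
| 0 (1 − 0.95²) | 9.75% |
| 0.33 | 9.5% |
| 0.5 | 9.1% |
| 0.7 | 8.3% |
| 0.8 | 7.8% |

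One pre-named visit, one averaged contrast or one 2-df joint test, in one unit, has 5%. To keep two separate visit tests at 5% overall, each would need 0.025 (Bonferroni), or about 0.026–0.031 if ρ of 0.33–0.8 is used.

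**3. What a single averaged contrast costs in power.** The sample-size inputs give a difference of 0.09 × 20.8 = 1.872 mL/kg/min with SD 4.0. Take 41 per arm (the final sample size before loss to follow-up) and r = 0.5 throughout.

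- One visit: residual variance factor 1 − 0.5² = 0.75; SD 4 × √0.75 = 3.46; SE 3.46 × √(2/41) = 0.765; ratio 1.872/0.765 = 2.45; power about 0.68.
- Average of two visits: factor (1 + 0.5)/2 − 0.5² = 0.50; SD 2.83; SE 0.625; ratio 3.00; power about 0.84.

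**4. Leaving sex out.** A sex-stratified trial with 50 per arm was simulated under no treatment effect and analysed by ANCOVA on baseline at one visit (10,000 runs per row). The article does not give the sex effect remaining after baseline adjustment, so a range is assumed. The last column is the mean model-based SE without sex relative to that with sex.

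| Residual sex effect (mL/kg/min) | Type I error, sex omitted | Type I error, sex included | SE ratio |
|---|---|---|---|
| 0 | 4.8% | 4.7% | 1.00 |
| 1 | 4.8% | 5.0% | 1.01 |
| 2 | 4.4% | 5.1% | 1.04 |
| 4 | 2.7% | 4.8% | 1.15 |

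Omitting the stratum lowers the error rate below nominal and does not raise it.

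**The case against.** The strongest reply is that the article describes one mixed-effects regression, and that the sample size rests on one interaction test. A joint or averaged test from that model has 5% error, and no sentence says that success may be claimed on either visit. This stands: the 8–10% applies only if the visits are tested separately. It does not remove the point, because a single model protects the error rate only when one contrast from it is named, and the article pairs two unranked primary visits with an express 5% for every test.

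A second reply is that an article may leave contrasts and covariates to a full analysis plan. That has force for the sex term, which is a one-line omission and no contradiction. It has less force for the primary test, where the article itself fixes both the two visits and the 5% rule.

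Two stronger readings are tempting, and the document supports neither.

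- A reader might count four primary tests (two visits by two units) and infer an error rate of up to about 15%. That needs L/min and mL/kg/min to be separate primary hypotheses. The units appear inside a measurement definition, the sample size uses mL/kg/min alone, and the article gives no correlation between the units.
- A reader might infer that ignoring the stratum adds to the false-positive rate. The simulation shows the opposite. Baseline VO2peak, already in the model, should also absorb much of the influence of sex.

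Finally, a visit average is one valid choice among several. The Introduction stresses adherence at 12 months, which an average dilutes.

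**Conclusion.** The point holds in a limited form. VO2peak is primary at two unranked visits, every test is at 5%, and no deciding contrast is named. If each visit is tested separately, the primary error rate is about 8–10% instead of 5%. The 9.5% end uses the article's own r = 0.5; the 7.8% end assumes a between-visit correlation of 0.8. If one joint or averaged test was always intended, the rate is 5% and the text only needs to say so.

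The missing sex term is a minor loss. Standard errors are about 0–4% too large for an assumed residual sex effect of up to 2 mL/kg/min, and about 15% too large at 4. It has no bearing on the inflated error rate. The unit is worth fixing for clarity, but the document does not establish that both units are primary tests.

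**What to change.** In Proposed Data Analyses:

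1. Name one primary contrast from the mixed model at two-sided 5%. For example, use HIIT minus MICT averaged over 6 and 12 months, then test 12 months and then 6 months, each only if the preceding test is significant. A single pre-named visit or a 2-df joint test would also control the error; the choice should follow the question the trial most wants answered.
2. State that the primary unit is mL/kg/min, as in the sample-size calculation, with L/min supportive.
3. Add sex as a fixed effect in the VO2peak and accelerometer models. The size of the gain was examined only for VO2peak; for accelerometry the reason is consistency with the stratified randomisation.
4. Declare that the contrast was chosen after data collection but before the treatment comparison was seen, if that is so. If it is not so, say that.

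The cost is a few sentences and one degree of freedom for sex. The downside is that visit-specific and L/min results lose primary status. The late date of the choice cannot be undone, only disclosed.
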